## Abstract

**Background:**

Dry eye is usually managed by conventional medical interventions such as artificial tears, anti-inflammatory drugs and surgical treatment. However, since dry eye is one of the most frequent ophthalmologic disorders, safer and more effective methods for its treatment are necessary, especially for vulnerable patients. Acupuncture has been widely used to treat patients with dry eye. Our aim is to evaluate the effectiveness and safety of acupuncture for this condition.

**Methods/Design:**

A randomised, patient-assessor blinded, sham (non-acupuncture point, shallow acupuncture) controlled study was established. Participants allocated to verum acupuncture and sham acupuncture groups will be treated three times weekly for three weeks for a total of nine sessions per participant. Seventeen points (GV23; bilateral BL2, GB4, TE23, Ex1 (Taiyang), ST1 and GB20; and left SP3, LU9, LU10 and HT8 for men, right for women) have been selected for the verum acupuncture; for the sham acupuncture, points have been selected that do not coincide with a classical acupuncture point and that are located close to the verum points, except in the case of the rim of the eye. Ocular surface disease index, tear film breakup time, the Schirmer I test, medication quantification scale and general assessment of improvement will be used as outcome variables for evaluating the effectiveness of acupuncture. Safety will also be assessed at every visit. Primary and secondary outcomes will be assessed four weeks after screening. All statistical analyses will be performed using analysis of covariance.

**Discussion:**

The results of this trial will be used as a basis for clarifying the efficacy of acupuncture for dry eye.

**Trial registration:**

ClinicalTrials.gov NCT00969280.

## Background

Dry eye is one of the most frequently occurring opthalmological health problems worldwide. The prevalence of dry eye is estimated to be in the range of 5% to 35% and its incidence has recently been increasing [1]. According to a recent survey, over 20% of outpatients in ophthalmologic clinics in Korea were diagnosed with dry eye [2]. The burden of dry eye involves not only problems with common activities such as reading, carrying out professional work, using the computer, watching television, and driving [3], but also widespread limitations in the activities of daily life, bodily pain, discomfort and lower energy and vitality [4].

Currently, the use of artificial tears and lifestyle modifications are the most common choices in management of patients with mild dry eye [5]. In moderate and severe cases, anti-inflammatory medications such as corticosteroids, cyclosporine and tetracycline are recommended [6]. However, preservatives in artificial tears may exacerbate ocular surface inflammation and the safety of anti-inflammatory treatment is not well established [6,7]. In this context, various treatments in complementary and alternative medicine (CAM) are administered for dry eye in clinical practice [8]. Acupuncture, one of the most popular CAM interventions, showed some favourable effects over artificial tears for dry eye when administered alone [9,10] or concomitantly [11,12] with artificial tears in several randomised controlled trials (RCTs). The evidence obtained from these trials is quite limited because all of these RCTs were conducted under high risk of bias including uncertainty of blinding, inadequate randomness of allocation of patients, failure to consider sample size and inappropriate control groups. Therefore, well-designed RCTs are needed to establish the efficacy of acupuncture for dry eye.

### Study aims

This study aims to evaluate the effectiveness and safety of acupuncture treatment for dry eye. The null hypothesis of this study is "the change in dry eye symptoms after verum acupuncture treatment is equal to the change in dry eye symptoms after sham acupuncture treatment."

## Methods/Design

This study is a randomised, patient-assessor blinded, sham acupuncture controlled trial. Enrolled participants will be randomly allocated to either a verum acupuncture or a sham acupuncture group and will receive nine sessions of treatment over a three-week period. Participants will be examined for signs and symptoms of dry eye before and after treatment (Figure 1).

**Figure 1 F1:**
[figure not shown]
**Study Flow Chart**.

### Recruitment

We will recruit participants by advertisements in local newspapers and on websites of local universities and companies in Daejeon province, Korea. Respondents will be contacted by clinical trial coordinators (CRC) to determine eligibility in a telephone pre-screening. If the applicant is eligible according to the study criteria, he or she will be invited to the clinical research centre of KIOM (Korea Institute of Oriental Medicine) and examined for eligibility by physicians and ophthalmologists.

### Inclusion and exclusion criteria

Eligible participants of both sexes who have moderate to severe levels of dry eye will be enrolled according to the inclusion and exclusion criteria. In addition to abnormal ophthalmological test results (Tear Film Break-Up Time and Schirmer I test), they must have symptoms of dry eye such as ocular itching, ocular foreign body sensation, ocular pain, ocular dryness, or vision problems, which may include blurred vision or a sensation of photophobia. Special medical conditions and conditions that can increase adverse event risk or might be expected to mislead interpretation of the outcome after acupuncture treatment comprise the exclusion criteria (Appendix 1).

### Sample size and randomisation

We wished to estimate the sample size that would suffice to detect an 18 point difference in the Ocular Surface Disease Index (OSDI) between the verum and control groups. In our previous uncontrolled acupuncture study, the standard deviation of OSDI was estimated to be 19.342 [13]. If we apply a two-sided 5% significance level, 90% power and 10% dropout rate, the calculated required sample size is approximately 21 participants in each group, according to the following equation:

An expert on statistics from KIOM who has no direct contact with the study participants will conduct randomisation of participants. He/she will generate random numbers with block randomisation using the SAS statistical package (Version 9.1.3; SAS institute Inc.). The block size will be concealed from other researchers and the randomisation table will not be available for assessment by anyone else involved in the study.

Opaque sealed envelopes containing serial numbers will be delivered to the clinical trial centre. Before the random assignment, all participants will be informed that they will be allocated to one of two groups. Random allocation will be conducted at visit 2. Random numbers with corresponding participants will be determined in the order of the time of second visit and will be opened by acupuncture practitioners. The allocation result will not be announced to the participants until the last visit of the last randomised participant.

The success of blinding will be assessed at each participant's last visit. Researchers who did not participate in the acupuncture treatment and who are blinded to the allocation results will perform the outcome assessment.

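### The stated inputs need about 27–29 participants per group for 90% power; 21 per group gives about 80%

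*Protocol article*

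**What the plan says.** All the inputs are in the protocol article, under Sample size and randomisation. The target is to "detect an 18 point difference in the Ocular Surface Disease Index (OSDI) between the verum and control groups". From an earlier uncontrolled acupuncture study, "the standard deviation of OSDI was estimated to be 19.342". The remaining inputs and the result come in one sentence: "two-sided 5% significance level, 90% power and 10% dropout rate, the calculated required sample size is approximately 21 participants in each group". The article then refers to an equation, which is not visible in the text available.

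Under Statistical analysis, the change from baseline to end of treatment is compared between groups by a two-sample t-test or Wilcoxon rank sum test. ANCOVA is used only if baseline characteristics turn out to be imbalanced. The abstract says instead that all analyses use ANCOVA. Neither place gives a baseline–outcome correlation, a one-sided test or any other power.

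**The concern.** Difference, SD, significance level, sidedness, power and dropout are all given, so the group size follows from them by arithmetic. It should come out at 21 and it does not: the number evaluable needed before any dropout allowance already exceeds 21.

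This calculation is the only justification given for the size of the trial, and it concerns the primary outcome. If the power is overstated, a non-significant result can be read as stronger evidence against an 18-point effect than the design can supply. The Background also criticises earlier trials for not considering sample size, so the article invites a check of its own figure.

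**Working it through.** **Inputs** (all from Sample size and randomisation): difference δ = 18; SD σ = 19.342, taken as common to both groups; two-sided α = 0.05; power 90%; dropout 10%; equal groups, implied by "approximately 21 participants in each group".

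**Formula.** Evaluable number per group: n = 2(z₁₋α/₂ + z₁₋β)² σ²/δ², with σ²/δ² = 19.342²/18² = 1.1547.

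**Attempt to reproduce 21 from the stated inputs**

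- 90% power, two-sided 5%: 2 × (1.960 + 1.282)² × 1.1547 = 24.27, so 25 evaluable.
- With 10% dropout: 24.27/0.9 = 26.96, so 27; or, rounding first, 25/0.9 = 27.8, so 28.
- Exact (noncentral t): 25.27, so 26 evaluable; 26/0.9 = 28.9, so 29 enrolled.

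The stated 21 is not reproduced. The total would be 54–58, against 2 × 21 = 42.

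**Other settings tried, to see what might lie behind 21** (normal approximation)

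| Setting | n before rounding | Evaluable | Enrolled with 10% dropout |
|---|---|---|---|
| Two-sided 5%, 80% power | 18.13 | 19 | 21 (18.13/0.9 = 20.1, or 19 × 1.1 = 20.9); 22 from 19/0.9 |
| Two-sided 5%, 85% power | 20.73 | 21 | 24 |
| One-sided 5%, 90% power | 19.78 | 20 | 22–23 |
| One-sample form, two-sided 5%, 90% power | 12.13 | 13 | 14–15 |

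Two-sided 80% power is the closest match. One-sided 5% at 90% power comes near, and its exact t figure is 21 if dropout is left out.

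**Power that 21 per group delivers for 18 points, two-sided 5%**

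| Evaluable per group | t-test | Normal approximation |
|---|---|---|
| 19 (21 × 0.9 = 18.9) | 79.7% | 81.8% |
| 21 (no dropout) | 83.7% | 85.4% |
| 25 | 89.7% | 90.8% |

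**Detectable difference.** With 19 evaluable per group, 90% power is reached at 20.9 points (t) or (1.960 + 1.282) × 19.342 × √(2/19) = 20.3 points (normal), not at 18.

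**What would rescue 90% with 19 evaluable.** The SD of the analysed variable would have to be about 17.1 (normal) or 16.7 (t) instead of 19.342. Under baseline-adjusted ANCOVA, with 19.342 as the SD at one time point, the variance is multiplied by 1 − ρ², so ρ = √(1 − 19/24.27) ≈ 0.47 is needed (normal; about 0.5 by t). For an unadjusted change score with the same SD at both times, the variance is multiplied by 2(1 − ρ); reaching 17.1 needs 2(1 − ρ) = (17.1/19.342)² = 0.78, so ρ ≈ 0.61. The article gives neither a smaller SD nor a correlation.

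**The case against.** The strongest objection is that the equation cannot be seen. It could contain a baseline adjustment: a correlation of about 0.47 would give 19 evaluable and about 21 enrolled at 90% power, and the abstract does speak of ANCOVA throughout. The unseen equation is not a fault of the plan, and the conclusion must be limited to the inputs stated in words. But those words include no correlation, and the Statistical analysis section makes ANCOVA conditional on imbalance, so the adjustment cannot be assumed.

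A second objection is that the cause is not established. This stands. The 80% route reaches 21 only with particular rounding, and a one-sided calculation truncated to 19 also lands near 21. Either explanation contradicts the stated two-sided 90%, so the defect is the same.

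A third is that the mismatch does not show whether the power or the group size is the wrong figure. This also stands, and it bears on the remedy. Finally, the word approximately cannot absorb a gap of 6–8 participants per group.

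**Conclusion.** The concern holds. From the inputs stated in the text, 90% power requires 25 evaluable and 27–28 enrolled per group by normal approximation, or 26 and 29 by exact t. The stated 21 falls short by 6–8 per group and gives about 80% power after the planned dropout. The type II risk for 18 points is about 20% rather than 10%.

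This rests on a common SD of 19.342 for the variable analysed, equal groups and an unadjusted two-sample comparison. If 19.342 is instead the SD of the score at one time point, the power of the change-score analysis depends on an unstated correlation: it equals the figures above at ρ = 0.5, and is lower below that value and higher above it. The arithmetic is certain; the reason for the slip is not.

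**What to change.** Keep 21 per group and correct the power statement, for example: about 80% power to detect an 18-point OSDI difference (SD 19.342, two-sided 5%) with 19 evaluable per group, allowing for 10% dropout. Say in the same place whether 19.342 is the SD of the OSDI score or of its change, since the analysis is on change.

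If baseline-adjusted ANCOVA is to be the primary analysis, give its power with the assumed correlation. As an illustration, ρ = 0.5 with 19.342 as the single-time SD gives 89.7% by t with 19 per group; that correlation is an assumption and needs a source.

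The cost is wording only: a less favourable power figure and no extra participants. If the sponsor does intend 90% power with the unadjusted comparison, the alternative is 27–29 per group, which is 12–16 more participants in total (54 − 42 to 58 − 42).

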### Acupuncture treatment protocol

Acupuncture of both groups will be carried out by licensed oriental medicine physicians who have been trained for four years and have at least five years of clinical experience in acupuncture treatment. Acupuncture practitioners will be required to attend a one-day training course on this study.

### Verum acupuncture group

Standardised acupuncture treatment will be applied to patients in the verum acupuncture group. Acupuncture points were selected according to the opinions of professional acupuncturists in KIOM based on a publication about acupuncture treatment for dry eye [14]. Seventeen acupuncture points represented by bilateral BL2, GB4, TE23, Ex 1 (Taiyang), ST1, and GB20 and unilateral SP3, LU9, LU10, HT8 and GV23 were chosen. For SP3, LU9, LU10, and HT8, males will be treated on the left side and females on the right side according to traditional Korean medicine theory. Disposable, 20 mm*30 mm-size acupuncture needles (Dongbang Co., Korea) will be used. With the exception of Ex1 (Taiyang), each point will be selected and treated in accordance with the WHO Standard Acupuncture Point Locations in the Western Pacific Regional guideline [15]. After insertion, needles will be twisted several times until the participants feel 'de qi' sensation and left for 20 minutes. Each participant will undergo a total of nine sessions (three times per week for three weeks).

### Sham acupuncture group (non-acupuncture point shallow penetration group)

A sham acupuncture point corresponding to each verum acupuncture point was selected. The principle of sham point selection is that the sham point should not be a classical acupuncture point and should, except for points on the rim of the eye, be located close to the verum point. The selected sham points are as follows: both points 2 cm lateral to ST4, 2 cm below ST7, at the parietal eminence of head, 2 cm internal to ST9, 10 cm internal to BL57, 1.5 cm internal to ST36, one point at the left middle point of the bicepsbrachii muscle belly, points at 2 cm, 4 cm, and 6 cm from the Lt. wrist fold, and one point located between the Lt. 3^rd ^and 4^th ^metatarsophalangeal joints. After shallow penetration of the skin at each site with no manipulation for 'de qi,' the needle is left for 20 minutes. Every participant in the sham acupuncture group will be treated three times per week for three weeks.

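### In women the unilateral limb needles are on opposite sides in the two arms, an avoidable cue that could unblind a participant who knows the side rule

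*Protocol article*

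**What the plan says.** The section on the verum group sets a side rule by sex: "For SP3, LU9, LU10, and HT8, males will be treated on the left side and females on the right side". The Methods/Design part of the abstract repeats it: "left SP3, LU9, LU10 and HT8 for men, right for women".

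The section on the sham group has no such rule. It names the left side for every unilateral sham point: "one point at the left middle point of the bicepsbrachii muscle belly", then "points at 2 cm, 4 cm, and 6 cm from the Lt. wrist fold", then "one point located between the Lt. 3^rd ^and 4^th ^metatarsophalangeal joints". The same section says that each verum point has a corresponding sham point, and that a sham point "should, except for points on the rim of the eye, be located close to the verum point".

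Men and women are both eligible: "Eligible participants of both sexes who have moderate to severe levels of dry eye will be enrolled". The trial is described as blinded for patients and assessors. Under Sample size and randomisation, participants are told before assignment that there are two groups, and an assessment of whether blinding worked is planned.

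**The concern.** Within a sex, the side of the limb needles should not depend on the arm. As written, it does not in men and it does in women. A participant can see which arm or foot is needled, and the cue recurs at all nine sessions.

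This matters because OSDI is a questionnaire that the participant completes, and the discomfort VAS and the patient's general assessment are also self-reported. If a woman can work out her arm, her expectations can enter the very outcomes on which the comparison rests.

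The mismatch also departs from the sham section's own principle. For a woman, a sham point on the left forearm or left foot is on the opposite limb from every verum limb point. The only exception that the section states is the rim of the eye.

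**Working it through.** **Point count.** The article gives 17 verum points.
- Verum: 6 bilateral × 2 + 4 unilateral limb points (SP3, LU9, LU10, HT8) + GV23 = 12 + 4 + 1 = 17. This reproduces the stated figure. GV23 is a single point outside the side rule.
- Sham: 6 bilateral × 2 + 1 biceps + 3 from the wrist fold + 1 foot = 12 + 1 + 3 + 1 = 17.

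The totals agree, as they should if each verum point has one sham counterpart. The number of needles is therefore not the problem.

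**Side by sex and arm (unilateral limb points).**

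| | Verum | Sham | Does side separate the arms? |
|---|---|---|---|
| Men | left, 4 of 4 | left, 5 of 5 | no |
| Women | right, 4 of 4 | left, 5 of 5 | completely |

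**What side tells an observer.** Let f be the share of women. The article does not give it, so a range is shown. Allocation is taken as 1:1, in line with 21 participants in each group. An observer who knows the verum side rule and uses side alone is right for every woman and for half of the men:

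P(correct) = f × 1 + (1 − f) × 0.5 = 0.5 + 0.5f

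| f | P(correct), rule known | Women among 2 × 21 = 42 |
|---|---|---|
| 0 | 0.50 | 0 |
| 0.25 | 0.625 | 10.5 |
| 0.50 | 0.75 | 21 |
| 0.75 | 0.875 | 31.5 |
| 1 | 1.00 | 42 |

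The last column counts participants in whom side differs by arm. It does not count participants who would be unblinded.

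For an observer who does not know the rule, P(correct) from side alone is 0.50 whatever f is. If side is matched between arms within each sex, it is 0.50 for everyone, informed or not.

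**Effect on the result.** The article gives neither the share of women, nor the proportion who know the rule, nor how far knowing the arm would shift OSDI. No bias in OSDI points can be derived.

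**The case against.** A reader might infer that the side needled reveals allocation in every woman. The article does not support that. Side is informative only to someone who knows the verum rule. Each participant experiences only her own treatment, and nothing says that the rule is disclosed to her. This objection stands: the threat is conditional. It does not vanish, because the article attributes the rule to traditional Korean medicine theory and prints it in its abstract, so a participant could already know it or come across it.

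A reader might also infer that assessor blinding is broken. That is not shown. Outcome assessors take no part in needling and are blinded to allocation, and the Schirmer and tear break-up tests are eye tests. Nothing says that hands or feet are inspected. Side could reach an assessor only through visible marks or a participant's remark. The practitioner who rates general improvement is a separate matter: practitioners open the allocation envelopes, so they know the arm whatever the side.

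A third tempting reading is that the share of women equals the share of the trial at risk. It does not. In both sexes the sham avoids the eye rim, is shallow, involves no manipulation for de qi, and adds bilateral leg points. Someone who has read the abstract could use some of these cues too, so the extra information from side may be modest, and matching the side leaves the other cues in place. However, the eye-rim difference is a declared exception, and shallow insertion without de qi defines this sham. The side difference is neither declared nor explained, and it can be removed.

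Finally, blinding will be assessed. That can detect a failure but cannot prevent one, and a result pooled over the sexes could hide a problem confined to women.

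That the article condenses a fuller protocol is no answer here, since it states the sham side explicitly.

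**Conclusion.** The point holds in a limited form. In women the side of the unilateral limb needles differs systematically between arms; in men it does not. This conflicts with the sham section's own placement principle and could unblind a woman who knows or learns the rule, in a trial whose primary outcome is patient-reported.

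The mismatch itself is certain on the text. Its consequence is not quantified. The guess probabilities of 0.50 to 1.00 assume 1:1 allocation and an observer who knows the rule and uses side alone. It remains an avoidable weakness in patient blinding, worth correcting because the correction costs almost nothing. It is not evidence that blinding has failed.

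**What to change.** Reconcile the verum and sham sections so that, within each sex, the unilateral points are on the same side in both arms. All five unilateral sham points need to be covered. What matters statistically is only that side does not depend on arm; which side is used is for the sponsor to settle.

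Include the reconciled rule in the one-day training that practitioners already attend. As a minor addition, report the planned blinding assessment separately for men and women.

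The cost is about one line in the sham description and one item in existing training. It needs no extra points, visits or staff. Reporting by sex needs only one more split of data already collected.

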### Permitted and prohibited concomitant treatments

Participants will be permitted to use artificial tears depending on symptom severity; the frequency and dosage of use must be recorded. However, the use of artificial tears during the two hours prior to acupuncture treatment will be prohibited. Drugs or tear supplements such as cyclosporine, corticosteroids, biological tear substitutes and oestrogen will be prohibited. The wearing of contact lenses will be prohibited during the trial period.

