### Primary outcome measurement

OSDI will be used as the primary outcome variable. This questionnaire is a 12-item instrument for assessment of ocular irritation and impact on visual function in dry eye sufferers. It can provide quantifiable results of dry eye symptom frequency and vision-related functioning [16]. Each question will be answered on a scale of 0 to 4, where 0 means none of the time; 1, some of the time; 2, half of the time; 3, most of the time; and 4, all of the time. Each patient's OSDI score will be calculated on the basis of the following formula: OSDI = [(sum of scores for all questions answered)*100]/[(total number of questions answered)*4]. We will use the Korean version of the OSDI questionnaire [17].

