### Secondary outcome measurement

The visual analogue scale (VAS) for self-assessment of ocular discomfort will be used. Self-reports on ocular symptoms concomitant with dry eye will be obtained for such conditions as ocular itching, foreign body sensation, burning, pain and dryness as well as for blurred vision, sensation of photophobia, ocular redness and sensation of tearing. Each participant will record a score indicating his or her total level of discomfort on a 100 mm horizontal line.

Tear Film Break-Up Time (TFBUT) and the Schirmer I test with anaesthesia will be used as additional secondary outcome variables. TFBUT is a method for observing tear film stability. Sodium fluorescein (2.5%) will be instilled in both eyes and the tear break-up time (the interval between the last complete blink and the first appearance of a dry spot or disruption in the tear film) will be measured [18]. The Schirmer I test with anaesthesia is a method for checking basic tear secretion. Schirmer test paper (Color Bar™ Eagle Vision, USA) will be inserted on the lateral third of the lower eyelid with the participant's eye closed for five minutes. Each test will be performed by a single ophthalmologist.

Medication Quantification Scale (MQS) and General Assessment of Improvement will also be used as secondary outcome variables. The total frequency and dosage of artificial tears will be checked. At the final visit of each participant, both participant and practitioner will assess improvements in ocular symptoms. 'Excellent' indicates the presence of no symptoms related to dry eye and much improvement in daily life; 'Good' means that a few symptoms related to dry eye are present but that the condition is better than before treatment; 'Fair' means that several symptoms related to dry eye are present but that the condition is a little improved; 'Poor' means that there is no change compared with before treatment; 'Aggravation' means that symptoms are worse than they were before treatment (Table 1).

**Table 1 T1:** Schedule for treatment and outcome measurement

Period	screening										F/U
Visit	1	2	3	4	5	6	7	8	9	10	11
Week		1st			2nd			3rd			Visit10+ 1 week+ 3 days
Informed consent	ν										
Demographic characteristics	ν										
Medical History	ν										
Physical examination	ν										
Random Allocation		ν									
Acupuncture Treatment		ν	ν	ν	ν	ν	ν	ν	ν	ν	
Symptom score	ν	ν	ν	ν	ν	ν	ν	ν	ν	ν	ν
OSDI		ν		ν			ν			ν	ν
Schirmer I test	ν									ν	
TFBUT	ν									ν	

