MQS		ν	ν	ν	ν	ν	ν	ν	ν	ν	ν
General assessment (patient/doctor)										ν	
Blinding Assessment		ν									ν
Safety Assessment		ν	ν	ν	ν	ν	ν	ν	ν	ν	ν

OSDI: Ocular Surface Disease Index; TFBUT: Tear Film Break-up Time; MQS: Medication Quantification Scale

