### Statistical analysis

We will conduct analysis on an intention-to-treat basis (significance level p < 0.05) using the SAS statistical package program (ver. 9.1.3). Baseline characteristics will be shown as mean ± standard deviation (SD) for continuous data including age, previous duration of dry eye, OSDI, VAS for self-assessment of ocular discomfort, TFBUT and Schirmer's I test value. As for participants' gender, n (%) of male and female in each group will be shown as baseline characteristics. We will conduct between-group comparision in baseline using two-sample t-test or Wilcoxon rank sum test for continuous data and using Chi-square test or Fisher's exact test for gender composition considering p < 0.05 as statistically significant.

For primary and secondary outcome measures, the mean differences from baseline values to the end of treatment will be compared using two-sample t-test or Wilcoxon rank sum test. If any imbalances in baseline characteristics between groups are encountered, we will conduct ANCOVA (analysis of covariance) using these imbalanced variables as covariates and allocated group as fixed factor.

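### Tear use may follow symptoms in both arms, but the analysis does not link it to OSDI, does not name it at baseline, and reduces it to two visits

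*Protocol article*

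**What the plan says.** All places are in the protocol article.

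- The section *Permitted and prohibited concomitant treatments* sets the rule on tears: "Participants will be permitted to use artificial tears depending on symptom severity; the frequency and dosage of use must be recorded". The next sentence gives the only restriction on artificial tears: "However, the use of artificial tears during the two hours prior to acupuncture treatment will be prohibited". No cap on amount is stated.
- *Primary outcome measurement*: "OSDI will be used as the primary outcome variable". The scoring formula uses the questionnaire items alone and has no term for tear use.
- *Secondary outcome measurement*: "Medication Quantification Scale (MQS) and General Assessment of Improvement will also be used as secondary outcome variables". The section then adds: "The total frequency and dosage of artificial tears will be checked". Table 1 schedules MQS at visits 2 to 11 and OSDI at visits 2, 4, 7, 10 and 11.
- *Statistical analysis*: the continuous baseline variables are described as "including age, previous duration of dry eye, OSDI, VAS for self-assessment of ocular discomfort, TFBUT and Schirmer's I test value", with gender handled separately. For all primary and secondary outcomes, "the mean differences from baseline values to the end of treatment will be compared using two-sample t-test or Wilcoxon rank sum test". ANCOVA follows only if a baseline imbalance is seen, with the imbalanced variables as covariates.

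**The concern.** Tear use is allowed to respond to symptoms, and symptoms are what OSDI measures. The *Background* section treats tears as an active therapy: a usual choice in mild disease and the comparator in earlier acupuncture trials. If verum needling works, some of its benefit may show as fewer tears and not as a lower OSDI score, while sham participants who stay symptomatic may take more tears and report a better score. Both movements pull the OSDI difference toward zero.

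The data that would show this are collected, but the stated analysis uses them thinly. OSDI and tear use are tested separately, and nothing says how one is to be read in the light of the other. Visit 2 tear use is not a named baseline variable. The change rule also passes over most of the MQS records. At stake is how a small or null OSDI difference would be interpreted.

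**Working it through.** **1. Does tear use enter the OSDI comparison?** The OSDI formula has no such term. The test is an unadjusted comparison of change. Covariates enter only through an observed baseline imbalance, and MQS is not among the named variables. As written, there is no link.

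**2. How much of the MQS record is used?** Table 1 gives ten MQS records, visits 2 to 11. Taking the end of treatment as visit 10, the last acupuncture session, a baseline-to-end change uses 2 of the 10. Visits 3 to 9 (seven records) and visit 11 do not enter. The *Secondary outcome measurement* section refers to a total, and a total over treatment is a different quantity from visit 10 minus visit 2.

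**3. The plan's own figure.** Inputs from *Sample size and randomisation*: difference 18, SD 19.342, two-sided 5%, power 90%, dropout 10%, about 21 per group.

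n per arm = 2 × [(1.960 + 1.282) × 19.342 / 18]² = 24.27, so 25. With dropout, 25 / 0.90 = 27.8, so 28.

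The stated 21 does not reproduce. That is a separate question and does not decide this one. I use 21 per arm as planned, and 21 × 0.90 = 18.9, so 19 per arm, after dropout.

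**4. Illustration of dilution (assumed inputs).** The documents give no effect of tears on OSDI. Suppose the share of participants who step up tear use is 20 to 40 percentage points higher under sham than under verum, and each gains 5 to 10 OSDI points from it.

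- Low: 0.20 × 5 = 1 point; 1 / 18 = 6% of the target.
- High: 0.40 × 10 = 4 points; 4 / 18 = 22% of the target.

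Power ≈ Φ(difference / [19.342 × √(2/n)] − 1.960). The standard error is 6.28 at n = 19 and 5.97 at n = 21.

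| Points lost | Difference left | Power, 19 per arm | Power, 21 per arm |
|---|---|---|---|
| 0 | 18 | Φ(0.91) = 82% | Φ(1.06) = 85% |
| 1 | 17 | Φ(0.75) = 77% | Φ(0.89) = 81% |
| 4 | 14 | Φ(0.27) = 61% | Φ(0.39) = 65% |

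This takes 19.342 as the SD of the quantity compared. It shows how little margin there is and does not estimate what will happen.

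**The case against.** The best defence is that comparing OSDI whatever tears are taken is a legitimate treatment-policy comparison under intention to treat, and that detail on concomitant use belongs in an analysis plan that is not shown. The first part stands: OSDI regardless of tear use should stay primary. The second stands in part. The article does fix a test and a change rule for every outcome, and that rule fits poorly with its own reference to a total.

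Four stronger readings are tempting, and the documents do not support them:

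- *Tears are unlimited.* They are barred for two hours before each session, and use must be recorded.
- *Tear use is ignored.* MQS is a secondary outcome compared between arms, so a benefit taken as fewer tears would be looked for there.
- *The imbalance rule cannot reach tear use.* The baseline list opens with the word *including*, so it is not closed, and the rule covers any baseline imbalance. The accurate statement is that visit 2 MQS is not named.
- *Tear use can mimic an acupuncture effect.* With randomisation and patient blinding, if needling does nothing then tear use differs between arms only by chance, which the 5% error already covers. A systematic difference would need failed blinding or influence from practitioners, who know the allocation. The documents give no sign of either.

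**Conclusion.** The point holds as a minor one. Symptom-driven tears with no stated cap on amount may dilute the OSDI difference. The stated analysis neither links the two nor names visit 2 MQS at baseline, and it would reduce ten MQS records to two.

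The size is unknown from the documents. The 1 to 4 point range rests wholly on assumed inputs and shows only that the design has little power to spare. The conclusion concerns masking. A reader might infer that a positive OSDI result would be untrustworthy, or that OSDI is the wrong primary outcome; neither follows.

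**What to change.** 1. Keep OSDI regardless of tear use as the primary comparison, and declare it as such.
2. Name visit 2 MQS as a baseline variable, stating that it covers use before the first needling. Include it, with baseline OSDI, as a prespecified covariate in the OSDI ANCOVA, run whatever the baseline comparison shows. The Abstract already promises ANCOVA throughout. This deals with chance baseline differences in tear use and may gain precision; it does not remove dilution.
3. Compare total tear use from after the first session to visit 10 between arms, adjusted for visit 2 use, and report it beside the OSDI result. If each record covers the time since the previous visit, this total comes from the eight records at visits 3 to 10. It is the part that lets a reader see whether benefit was taken as fewer tears.

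Two things to avoid. Do not adjust OSDI for tear use after randomisation: it may itself be an effect of treatment, and adjusting for it would bias the comparison. Do not replace OSDI with a composite that ranks any rise in tear use below every other outcome, because a trivial rise would then outweigh a large OSDI gain.

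The cost is wording, one or two covariates in a small trial and one more secondary result. No new data are needed, and nothing about permitted tear use changes.
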